### Data Analysis

For the main analysis of this study (evaluating the efficacy of SocialVille as a treatment for social cognition deficits) we will define an Intent-To-Treat (ITT) population that includes all participants who have been randomized to either group. We will compare treatment and active control groups in the ITT population to determine if any differences in baseline demographic, characterization, outcomes variables, or total program use time remain after the randomization process.

We will test the following hypotheses of the primary outcomes, in addition to exploratory analyses: (1) Experimental treatment versus active control improves social cognition, and (2) Experimental treatment versus active control improves functional capacity. In addition, we will test the following hypotheses of the secondary outcomes: (1) Experimental treatment versus active control improves symptom severity; (2) Experimental treatment versus active control improves functioning; (3) Experimental treatment versus active control improves social cognition; (4) Experimental treatment versus active control improves motivation, and (5) Experimental treatment versus active control improves quality of life.

To examine each hypothesis, we will examine the data from each outcome measure(s) associated with the Primary or Secondary outcomes using a linear mixed-effects model with group and time as fixed factors, site as a random factor, and additional factors/covariates as required if there are trends towards significant baseline differences (p < 0.1) in the treatment and active control groups. Missing data will be handled with an iterative maximum likelihood procedure to optimally estimate model parameters. The key value for significance will be the group-by-time interaction term. This modeling will be conducted with a Type I error set at 0.025 for each model.

In addition, to identify variables that predict treatment success in the SocialVille group, we will use an individual differences approach [80] and test for associations between not only outcome variables and pre-test scores (raw and composite), but also between outcome variables and improvements in aspects of the training tasks. This will help us determine if specific types of patients benefit from training more than others as well as if particular improvement patterns on training (i.e., training strategies) are predictive of successful outcomes. These analyses will be evaluated after correcting for multiple comparisons (i.e., Bonferroni).

Finally, following the main analyses, we will construct two separate composites, of low-level and high-level SC assessments, respectively, and test the effects of training on each of these composites using a linear mixed-effects model. We will further examine correlations between magnitude of change on each of the constructs and % improvement on SocialVille exercises.

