### Randomization

Participants will be randomized after the last baseline visit (V2) and before the planned program set-up visit (V3), which is the first day of program use. All V0-V2 data for each participant must be fully monitored, with all queries resolved, before randomization may take place.

Given the potential importance of cognitive abilities on the response to social cognitive training, participants will be stratified by gender, education (<13 years, >13 years) and age (18–40 years, 41–65 years) and randomly assigned to either treatment (SocialVille) or active control group at each site with an allocation ratio of 1:1. We will employ a minimization method of adaptive stratified randomization (referred to as the ‘platinum standard’ of randomization methods when stratification is required) to minimize the imbalance between the number of participants in each group over these factors.

For this trial, we will use a secure randomization server (Sealed Envelope) that implements the specified procedure and an unblinded study member Site Coordinating Center will issue a randomization assignment at the appropriate time. This approach represents a best practice approach to randomization, implementing an automated centralized group assignment procedure with allocation concealment, and effective separation of sequence generation and allocation concealment.

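### Choosing covariates by baseline tests at p < 0.1 leaves the co-primary models open until the data are seen and in practice shuts out the minimisation factors; programme use time should be barred explicitly

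*Protocol article*

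**What the plan says.** The Data Analysis section specifies a "linear mixed-effects model with group and time as fixed factors, site as a random factor", plus "additional factors/covariates as required if there are trends towards significant baseline differences (p < 0.1"). The test is the group-by-time interaction, at 0.025 for each model. No other baseline variable is fixed in advance.

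The same section says that the arms will be compared for "differences in baseline demographic, characterization, outcomes variables, or total program use time remain after the randomization process".

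The Randomization section says "We will employ a minimization method of adaptive stratified randomization" and that "participants will be stratified by gender, education (<13 years, >13 years) and age (18–40 years, 41–65 years"), with 1:1 allocation at each site. The reason given is "Given the potential importance of cognitive abilities on the response to social cognitive training". The same section places randomisation before the set-up visit (V3), which it identifies as the day on which programme use begins.

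**The concern.** Three features of the stated analysis do not fit the stated design.

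- **The model is not fixed.** Which covariates enter either co-primary model depends on baseline tests. In a properly randomised trial a baseline p < 0.1 is a chance event and says nothing about whether the variable predicts outcome. The rule can add irrelevant variables and omit relevant ones.
- **The design factors are passed over.** Gender, education and age are treated as important enough to balance at allocation but are not in the analysis model. The only route into the model is a significant imbalance, which minimisation exists to prevent. If these factors predict change, an analysis that ignores them overstates the standard error and gives away precision that the design has secured.
- **Use time is misplaced.** A quantity that accrues only after randomisation cannot be a difference left over from randomisation. It may be a consequence of the assigned programme. Adjusting for it would condition the intention-to-treat comparison on a post-randomisation outcome.

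**Working it through.** **Inputs from the protocol article:** d = 0.50 on the change score and 128 completers, 64 per arm (Power Calculation; Overall Design); 0.025 per model, threshold p < 0.1, group-by-time test (Data Analysis); minimisation on three factors (Randomization). **Assumed:** two-sided 0.025, since sidedness is not stated; the share R² of the variance of change explained by the three factors, for which the article gives no figure; the number of baseline tests.

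**1. The plan's own sample size.** With n per arm = 2(z₁₋α/₂ + z₁₋β)²/d², two-sided 0.05 and 80% power (target not stated), n = 2(1.960 + 0.842)²/0.25 = 62.8, so 63. With 64 per arm the t-test power is 0.80, so 128 reproduces. At two-sided 0.025, 64 per arm gives about 0.72 (normal approximation; 0.71 by t-test). That is the starting level for the power figures in step 4.

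**2. How often chance alone triggers the rule.** For k independent tests, P(at least one p < 0.1) = 1 − 0.9^k:
- k = 5: 41%
- k = 10: 65%
- k = 20: 88%

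The article does not state k. Baseline variables are correlated, so these are indicative only.

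**3. Whether a minimised factor can be flagged.** Take 64 per arm and a factor split evenly overall. A 36/28 against 28/36 table gives χ² = 128(36² − 28²)²/64⁴ = 2.0, p = 0.16. A 37/27 against 27/37 table gives χ² = 128(37² − 27²)²/64⁴ = 3.1, p = 0.08. The arms must therefore differ by about 10 people on one factor level before it is flagged. In a simulation with n = 128, three evenly split binary factors, a biased coin of 0.9 (assumed), no site level and 3,000 runs per scenario, a minimisation factor reached p < 0.1 in 0% of runs.

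**4. Consequence if the factors predict change.** With the factors balanced, the true standard error is √(2/64) × √(1 − R²) = 0.1768√(1 − R²), while the unadjusted model reports about 0.1768.
- Type I error: 2[1 − Φ(2.241/√(1 − R²))]
- Power without adjustment: Φ[(0.50 − 2.241 × 0.1768)/(0.1768√(1 − R²))]
- Power with adjustment: Φ[0.50/(0.1768√(1 − R²)) − 2.241]

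| R² (assumed) | SE too large by | Type I error | Power, unadjusted | Power, adjusted |
|---|---|---|---|---|
| 0.10 | 5% | 0.018 | 73.2% | 77.0% |
| 0.20 | 12% | 0.012 | 74.4% | 82.1% |

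The gain is 3.8 and 7.7 points. The simulation in step 3 gave type I error 0.018 and 0.012, and power of 73% against 77% and 74% against 81%. A separate simulation gave type I error of about 0.017 and 0.009.

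**5. Consequence if the factors affect level only.** The interaction compares changes, so a constant effect on level cancels. In 4,000 simulated trials for each R², with the factors explaining 10% or 20% of level and none of change, unadjusted and adjusted type I errors were 0.029 and 0.030 (10%) and 0.031 for both (20%), with Monte Carlo error about 0.0025. Mean standard errors were 0.1365 against 0.1366 and 0.1367 against 0.1368. Nothing is lost.

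**6. The form of adjustment matters.** With complete data, adding a time-constant covariate as a main effect leaves the interaction as it was: in a check, 0.45203 (SE 0.19264) with and without it. With covariate-by-time terms it became 0.43102 (SE 0.18811). Entering the baseline score as a covariate while baseline is also a response is not a remedy. In another check it left the estimate identical but shrank the SE from 0.11698 to 0.1115, because the same data stood on both sides.

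**7. Order of events.** The last baseline visit is V2, randomisation follows, and V3 is the first day of use. Use time is therefore zero for everyone at baseline.

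**The case against.** The strongest reply is that the test is a difference in change. Gender, education and age group are constant over time, so a plain effect on score level drops out, and the article gives no figure for how far they predict change. This stands. The loss in step 4 is conditional, and the stated reason for balancing speaks only of potential importance for response. Where the loss occurs it is in the conservative direction. It is also true that selecting genuine baseline covariates by p < 0.1 does not in itself bias the estimate.

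A reader might infer more from the use-time wording, namely that the plan adjusts for use time and so biases the effect. In simulated scenarios (arms differing by 0.25 to 0.5 SD in use, slope 0.3, all assumed) a true 0.50 moved to between 0.30 and 0.70, with the direction depending on which arm used more. The document does not support that reading. The covariate rule is worded for differences at baseline, use time appears in a separate sentence about comparing the arms, and nowhere is it said to enter the model. The size of any shift rests wholly on invented inputs. What remains is that use time stands in one list with baseline variables just before the covariate rule, and nothing excludes it.

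Nor is this a matter of detail left to an analysis plan: the article states the selection rule and the threshold.

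**Conclusion.** The concern holds in a limited form. The p < 0.1 rule makes both co-primary models data-dependent, selects on chance imbalance, and in practice excludes the three factors used in minimisation. If those factors explain 10% to 20% of the variance of change, the stated analysis runs at a type I error of about 0.01 to 0.02 instead of 0.025 and loses about 4 to 8 points of power, at two-sided 0.025 with 64 per arm. If they act on level only, it loses nothing. A claim of inflated type I error or of a biased effect is not supported. Use time is wrongly grouped with baseline differences and needs an explicit exclusion, but it is not shown to be a planned covariate.

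A minor separate slip: the education strata as written place a person with exactly 13 years in neither group.

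**What to change.** - Delete the p < 0.1 rule and report baseline characteristics descriptively, without tests.
- Keep site as planned. Pre-specify gender, education group and age group in every model, with factor-by-time terms in the group-by-time model. Alternatively, model the follow-up scores on the baseline score plus these factors. Do not use baseline as both a response and a covariate.
- Report total programme use time only as adherence, and state that it will not enter the intention-to-treat model.
- Define the education strata so that exactly 13 years falls in one group, and record how any such participants already randomised were classed.

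The cost is a few degrees of freedom and changes of wording. The Trial Status section says that recruitment is under way, so the changes should be fixed and dated before any unblinded look at outcomes.

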### Power Calculation for Sample Size

With the aim of having 128 participants complete the study, we have statistically powered it to detect a between-groups Cohen’s d effect size of 0.50 on an outcome measure, calculated as the between-group difference in the treatment effect means (post-assessment score minus pre-assessment score) divided by the pooled standard deviation of the observed test-retest reliability. This effect size translates, for example, in an improvement of 5.8 points (on an IQ-like index score) within the treatment group versus an improvement of 1.0 point within the active control group, with both groups showing a variance of 10 points (2/3 of a standard deviation, as observed in other composite cognitive performance data) from pre-assessment to post-assessment. The results of our feasibility study [80] allowed us to derive training group effect sizes; these ranged from 0.45-1.1 on the SocialVille measures, from 0.53-0.77 for the social cognitive measures and from 0.4-0.67 for the generalization and functional measures. A recent study conducted by our study collaborator, [name] [61] employed computerized social cognitive training and found effect sizes of 0.53 on the MSCEIT [94] perceiving emotions total subscale. Furthermore, a recent meta-analysis conducted on social cognitive training interventions in schizophrenia [68] found moderate to large effect sizes on facial affect recognition (Cohen’s d between 0.71-1.01) and small to moderate effect sizes on ToM (0.46). Effect size for total symptoms was found to be moderate to large (0.68). We therefore believe this is a reasonable estimate of the plausible effect size in the suggested trial, and that documentation of a 0.5 between-groups effect size in this trial would provide reasonable support for clinical benefit in this population.

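### The plan does not say how covariates added for baseline imbalance enter the model; as listed, without a time interaction, they do little to the group-by-time test

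*Protocol article*

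**What the plan says.** All of the modelling text is in the Data Analysis section of the protocol article.

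- Model: a "linear mixed-effects model with group and time as fixed factors, site as a random factor", with "additional factors/covariates as required if there are trends towards significant baseline differences (p < 0.1".
- Screening: the arms are compared to see if any "differences in baseline demographic, characterization, outcomes variables, or total program use time remain after the randomization process". Baseline outcome scores are therefore among the variables that can trigger adjustment.
- Deciding term: "The key value for significance will be the group-by-time interaction term".
- Missing data: "Missing data will be handled with an iterative maximum likelihood procedure to optimally estimate model parameters".
- Error rate: "This modeling will be conducted with a Type I error set at 0.025 for each model".

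The Power Calculation section defines the effect on the same contrast, as the "between-group difference in the treatment effect means (post-assessment score minus pre-assessment score" change, scaled to a Cohen's d of 0.50. No covariate-by-time term is named anywhere. No passage says that such terms are excluded.

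**The concern.** The plan pairs a remedy (covariates when the arms differ at baseline) with a test (group-by-time), and the remedy as listed does not reach the test. A baseline covariate is constant over a participant's visits. As a plain term it shifts all of that participant's visits by the same amount, and the shift cancels from the pre-to-post contrast.

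This matters only where the imbalanced covariate is related to change. The baseline outcome score always is, unless it is perfectly reliable: the arm that starts lower by chance tends to gain more on retest. If the rule is followed as listed, a co-primary result could be described as adjusted for baseline differences when the deciding estimate has hardly moved. How covariates are selected is a separate question; this point concerns what they do once added.

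**Working it through.** **Inputs**
- 64 completers per arm (Overall Design and Timeline; Power Calculation).
- Target d = 0.50 on change. Spread of change 10 points, described as 2/3 of a standard deviation, so score SD = 10 ÷ (2/3) = 15 (Power Calculation). The text calls the 10 points a variance; it is used here as an SD, the only reading that fits the 2/3.
- UPSA test-retest reliability 0.63 to 0.80 (Functional Capacity Outcome Measure).
- Trigger p < 0.1; Type I error 0.025 per model, taken as two-sided because the sidedness is not stated (Data Analysis).

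**1. The plan's own figure.** n per arm = 2(1.960 + 0.842)² ÷ 0.50² = 62.8, so 63; the t-test version gives 64, or 128 in total. That reproduces the target at two-sided 0.05 (or one-sided 0.025) and 80% power. It does not depend on the covariate rule.

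**2. Cancellation.** Write the score of participant i at visit t as Y(it) = group + time + group×time + βx(i) + participant effect + error. Then Y(i,post) − Y(i,pre) contains βx(i) − βx(i) = 0. A term γ(t)x(i) would instead leave [γ(post) − γ(pre)]x(i) in the change, which is where adjustment can act.

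**3. Simulation check** (three visits, 64 per arm, maximum likelihood; covariate strengths, dropout and number of sites are assumptions). Group-by-time at the last visit, one complete dataset, participant random intercept:

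| Added term | Estimate | SE | p |
|---|---|---|---|
| none | 2.822 | 1.941 | 0.146 |
| covariate, plain | 2.822 | 1.941 | 0.146 |
| covariate × time | 1.297 | 1.992 | 0.515 |
| baseline score, plain | 2.822 | 1.941 | 0.146 |
| baseline score × time | 3.464 | 1.867 | 0.064 |

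The two plain terms changed nothing in any of three complete datasets.

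- *Dropout, participant intercept.* A plain covariate moved the estimate from 0.222 to 0.180, 1.987 to 1.982 and 0.902 to 0.754 (SEs about 2.1 to 2.2). A plain baseline score moved it from 0.222 to −0.597, 1.987 to 1.630 and 0.902 to 0.850. The largest of these moves is 0.819, about 0.4 of an SE (0.819 ÷ 2.121).
- *Site as the only random effect, complete data.* The estimate stayed at 2.822, but the SE fell from 3.264 to 3.179 (covariate) or 2.224 (baseline score).
- *Site only, with dropout.* A plain baseline score moved the estimate more, for example from 2.740 to −0.672. That model ignores the correlation between a participant's visits, so it is a poor basis for judging the rule.

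**4. Size of what is left, for the baseline score**
- Gap at the trigger: 1.645 × √(2/64) = 0.291 SD, or 4.36 points (0.293 SD with the t quantile).
- Reliability implied by the power section: 10² = 2 × 15² × (1 − ρ), so ρ = 1 − 100/450 = 0.78.
- Spurious difference in change: (1 − ρ) × gap = 0.222 × 4.36 = 0.97 points; ÷ 10 gives d = 0.097. The worked example in the power section targets 5.8 − 1.0 = 4.8 points.
- Correlation of baseline with change: −√((1 − ρ)/2) = −0.33.
- Error given that gap, no true effect: the statistic has mean 0.333 × 1.645 = 0.548 and SD √(1 − 0.333²) = 0.943. Against ±2.241, the tails are Φ(−1.796) + Φ(−2.958) = 0.0363 + 0.0015 = 3.8%.

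| ρ | SD of change | Spurious points | d | Error given the gap |
|---|---|---|---|---|
| 0.80 | 9.49 | 0.87 | 0.092 | 3.7% |
| 0.78 | 10.00 | 0.97 | 0.097 | 3.8% |
| 0.63 | 12.90 | 1.61 | 0.125 | 4.5% |

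With the t quantile for the gap, the last row becomes d = 0.126 and 4.6%.

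**The case against.** The strongest reply is that the article never says covariates are left uncrossed. Its list of terms is shorthand: it names group and time without listing their interaction, although that interaction is the test, and it names no participant effect. A list that omits the primary interaction cannot prove that others are absent, and parameterisation is ordinary content for an analysis plan that is not shown. This stands as a limit on the wording. A reader might infer that the plan prescribes uncrossed covariates; the text is silent, and crossing is not excluded. The point survives because the article states a remedy and a test together, and the remedy, applied as listed, does not do its job.

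Three stronger readings also fail.
- *The covariate does nothing at all.* Exact invariance of estimate and SE needs complete data and a participant-level effect. The plan expects attrition (Weaknesses) and names only site as random, so the estimate or its SE can move.
- *Any imbalance stays uncorrected.* Imbalance that affects only the level of the outcome is already removed by the pre-to-post contrast.
- *The trial's Type I error is inflated.* The 3.7–4.6% applies given a gap at the trigger. Averaged over randomisation, this mechanism does not inflate the error rate.

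The article also expects most baseline measures not to separate responders, except potentially symptom severity (Aims and hypotheses), and minimises on gender, education and age (Randomization), which makes imbalance in those factors less likely. That weakens the case for ordinary covariates. It does not reach baseline outcome scores, which are screened and are tied to change through regression to the mean.

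**Conclusion.** The concern holds in conditional form. The Data Analysis section leaves the form of added covariates open; if they are plain terms, as listed, the imbalance rule does little for the test that decides the trial. For a baseline-score gap just at the trigger, the uncorrected bias is about d = 0.10 (0.09 to 0.13 over the UPSA reliability range), roughly a fifth to a quarter of the 0.50 target. Larger gaps leave more.

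The size rests on 64 per arm, equal score variances before and after training, the power section's 10 points read as an SD of change on a score SD of 15, and a two-sided 0.025 test. For other covariates it depends on a correlation with change that the document does not give. The invariance of the complete-data estimate does not depend on these assumptions.

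**What to change.** In the Data Analysis section, state that each baseline covariate in the co-primary and secondary models enters with its covariate-by-time interaction, alongside group, time and group-by-time. Limit this to true baseline variables; total program use time accrues after randomisation and should not be among them.

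Handle the baseline outcome score by an ANCOVA-type model: post-baseline or change scores as the response, adjusted for baseline, with the group contrast at the final visit as the deciding term. Baseline should not then also be one of the response visits.

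The cost is about one sentence of wording and, with three visits and time as a factor, two degrees of freedom per covariate. No new data or participants are needed.

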### Repeated Assessment Battery (Outcome Measures)

Once a participant is deemed eligible for participation based on their V0 results, they are next scheduled for their baseline sessions on the repeated assessment battery (V1-V2), which take approximately four hours total. After completing these baseline assessments, participants are randomly assigned to either experimental or control training conditions (see below). Then, after half of the training is completed (20 sessions), participants are given the repeated assessment battery (V4-V5), and again at the completion of the entire training protocol (20 additional sessions for a total of 40 sessions; V6-V7).

We will employ a battery of neuropsychological and functional assessments (see Table 3), measuring a range of parameters from proximal to very distal from program use (e.g., assessment of functional abilities and quality of life). This structure will allow us to determine the degree of transfer of benefit to untrained modalities, including the extent to which improvements generalize to untrained functional ability and real-world experience (e.g., quality of life). Assessments will be administered to all participants, including those enrolled in treatment and active control groups; alternate forms of the assessments will be used when available to mitigate test-retest effects. Site psychometricians conducting the assessments will be blinded to group allocation and will receive training by a member of the coordinating center staff regarding appropriate administration of all measures, scoring and data reporting to ensure data quality. Performance on all measures will be scored, submitted by the participating site into the study database, and monitored for accuracy and integrity by the Coordinating Center.

**Table 3 Tab3:** TRuSST Study primary and secondary outcome measures

Domain	Outcome measure
*Co-Primary Outcome Measures*	
Social Cognition	Penn Emotion Recognition Test (ER40)
	Prosody Identification (PROID)
	Penn Facial Memory Test (PFMT)
	MSCEIT-managing emotions subscale
	The Empathic Accuracy (EA)
Functional Capacity	The UCSD Performance-based Skills Assessment (UPSA-2)
*Secondary Outcome Measures*	
Symptom Severity	Positive and Negative Syndrome Scale (PANSS)
Functioning	Global Functioning Scale
	Social Functioning Scale
	The Specific Levels of Function (SLOF)
	VRFCAT
Social Cognition	The Awareness of Social Inference Test (TASIT), Part 3
	The Morphed Faces Task The Faux Pas Test

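### The deciding test is the group-by-time interaction over what appear to be three visits, which does not isolate the post-minus-pre contrast the trial was sized on, and baseline adjustment is triggered by a test instead of prespecified

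*Protocol article*

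**What the plan says.** The Data Analysis section of the protocol article specifies a linear mixed model with arm and time as fixed factors and site as a random one. It fixes the decision term: "The key value for significance will be the group-by-time interaction term". Type I error is 0.025 per model, with no statement of one or two sides. Further covariates enter only where a comparison of the arms at baseline gives p < 0.1; the variables compared include the outcome measures.

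The Repeated Assessment Battery section places a full assessment between baseline and the end of training: "after half of the training is completed (20 sessions), participants are given the repeated assessment battery (V4-V5"). With baseline (V1-V2) and post-training (V6-V7), each outcome is measured three times.

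The Power Calculation section describes a different quantity. The trial is sized for d = 0.50, "calculated as the between-group difference in the treatment effect means (post-assessment score minus pre-assessment score"). That is a single pre-to-post contrast, with no role for the mid-training visit.

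**The concern.** With three levels of time and two arms, the interaction has (3 − 1) × (2 − 1) = 2 degrees of freedom. It tests whether the two profiles differ in any way. It does not ask whether SocialVille is better at the end of training, which is what the hypotheses and the sample size concern. Two things follow. A significant result could come from a transient mid-training difference. And the power of the deciding test is not the power that was planned.

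Baseline handling is a second, smaller matter. Adjustment is switched on by a significance test on the trial's own data, so the form of the primary model is not known in advance. The baseline score is collected on everyone and could be used in every case.

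**Working it through.** **Inputs.** From the Power Calculation section: "With the aim of having 128 participants complete the study", hence 64 per arm at 1:1; d = 0.50; a worked example of 5.8 against 1.0 points; and "both groups showing a variance of 10 points (2/3 of a standard deviation"). The last figure is read as a standard deviation of change, because (5.8 − 1.0)/10 = 0.48 is close to 0.50. If 10 points is 2/3 of a standard deviation, the cross-sectional SD is 15. From 10² = 2 × 15² × (1 − ρ), the pre-post correlation is ρ = 1 − 100/450 = 0.778. A d of 0.50 is then 5 points.

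**Assumptions not in the article.** All three visits enter as levels of a factor, every pair of visits correlates at 0.778, data are complete, and there is no site effect.

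**Step 1: the plan's own figure.** A two-sample t-test on change with d = 0.50 and 80% power needs 64 per arm at alpha 0.05 two-sided (the same as 0.025 one-sided), which reproduces 128. At 0.025 two-sided it needs 78 per arm, and 64 per arm gives power 0.712. That drop from 80% to 71% comes from alpha, not from the choice of test.

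**Step 2: the 2-df test.** Let δ be the arm differences in (mid − baseline, post − baseline). Each change has variance 100 and their covariance is 15² × (1 − 0.778) = 50. The noncentrality is λ = (64/2) × δ′Σ⁻¹δ, referred to F(2, 125).

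- δ = (2.5, 5): δ′Σ⁻¹δ = (625 − 1250 + 2500)/7500 = 0.25, so λ = 8.0.
- δ = (5, 5): (2500 − 2500 + 2500)/7500 = 0.333, so λ = 10.67.
- δ = (5, 0): 2500/7500 = 0.333, so λ = 10.67.
- δ = (2.5, 0): 625/7500 = 0.083, so λ = 2.67.

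| True difference (mid, post), points | 2-df test, alpha 0.025 | 1-df post contrast, alpha 0.025 two-sided |
|---|---|---|
| 2.5, 5 (half present at mid) | 0.601 | 0.712 |
| 5, 5 (all present at mid) | 0.750 | 0.712 |
| 5, 0 (mid only) | 0.750 | no true post effect |
| 2.5, 0 (mid only, half size) | 0.195 (0.193 simulated) | no true post effect |

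At alpha 0.05 the first two rows become 0.706 and 0.832, against 0.801. For 80% power at 0.025, the 2-df test needs 94 per arm in the first case and 71 in the second; the post contrast needs 78.

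**Step 3: what a significant term would show.** In 20,000 simulated trials with a 5-point mid-only effect, 75% had a significant interaction. In 74% of all trials it was significant without a significant post-training benefit, and in 38% it was significant with a post estimate at or below zero. For a 2.5-point mid-only effect the corresponding figures are 19%, 18% and 9%.

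**Step 4: baseline adjustment.** Relative to a change score, adjusting for baseline multiplies the variance of the post contrast by (1 + ρ)/2 = 0.889, a cut of 11%. The effective d is 0.50/√0.889 = 0.530. Power rises from 0.712 to 0.767 at 0.025, and 69 per arm would reach 80%. Over the UPSA-2 reliability range of 0.63 to 0.80 the variance factor is 0.815 to 0.90. The lower end comes from follow-up of up to 36 months, longer than this trial.

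**Step 5: sensitivity.** If the mid visit correlates at 0.85 with the other two, the 2-df results become 0.601 (half at mid), 0.832 (all at mid) and 0.956 (5 points at mid only).

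**The case against.** The strongest reply is that the 2-df test is inferred. The article gives no degrees of freedom and does not list the visits in the primary model. If only pre and post enter, the interaction is exactly the contrast that was powered, and the first half of the point falls away. A condensed article may also leave contrast wording to an analysis plan. This stands as a limit on certainty. It does not remove the point: the article itself names the deciding term, and a time factor in a three-visit design has three levels unless something says otherwise.

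Several stronger readings are tempting, and the document does not support them.

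- *A result favouring the active control would count as success.* The F test has no direction, but the hypotheses in the Data Analysis and Aims sections do: they predict improvement and greater gains with SocialVille. Direction is partly handled, though not in the decision rule.
- *Baseline is left unadjusted.* Adjustment is conditional, not absent. The fair criticism is that a test at p < 0.1 decides it.
- *Power is always lost.* The article gives no mid-training effect. Under an early plateau the 2-df test does better than the unadjusted post contrast (75% against 71%).
- *The trial would usually be declared positive on a transient effect.* The 75% figure needs a full d = 0.50 at mid-training to vanish while the same training continues for 20 more sessions. Nothing in the article suggests this; at half the size the figure is 19%.

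The model as stated is also valid under randomisation. Baseline adjustment is a modest gain in efficiency and prespecification, not the repair of a bias.

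**Conclusion.** The point holds in a limited form. On the natural reading, the test that decides the trial is not the contrast that sized it, and its significance would not by itself establish a benefit at the end of training. The effect on power can go either way: 11 percentage points lower than the post contrast (60% against 71%) if half the effect is present at mid-training, 4 points higher (75% against 71%) if all of it is. Making baseline adjustment unconditional is worth about 6 points (71% to 77%). These figures rest on 64 complete cases per arm, two-sided alpha 0.025 for the single contrast, an SD of change of 10 points and equal correlations of 0.78. The point would shrink to its baseline part if the sponsor confirms that only pre and post enter the primary model; in that case one sentence saying so is needed.

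**What to change.** Name as the primary test, for each co-primary outcome, the 1-df between-arm difference at V6-V7 from the repeated-measures model. Always include the baseline outcome as a covariate (with mid and post as the responses), or constrain the baseline means to be equal across arms, and drop the p < 0.1 trigger for it. State that success requires the estimate to favour SocialVille. Report the mid-training contrast and the overall interaction as supportive.

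This changes analysis wording only: no added visits, data or participants. The costs are that an effect confined to mid-training no longer counts as success, and that some power may be given up if the full effect is already present at mid-training. Without baseline adjustment that is 71% against 75%. With it, the single contrast reaches 77% under equal correlations, but would trail the 2-df test (77% against 83%) if the mid visit correlates at 0.85 with the others.
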